## Abstract

**Background/Objectives:** Children who suffer from congenital heart defects (CHDs) have a decreased ability to perform physical exercise and consequently have a decrease in their functional capacity. The main causes of this decrease in functional capacity have been related on the one hand to residual hemodynamic defects and, at the same time, to a situation of physical deconditioning due to inactivity, as well as problems in lung function, especially the presence of restrictive patterns that influence the amount of O_2_ insufflated (decreased maximum VO_2_), consequently generating a deficient maximum O_2_ consumption and maximum work rate. This represents an important prognostic value, since it constitutes an independent predictor of death and hospitalization. This study aims to determine the benefits obtained regarding respiratory function, exercise capacity, and quality of life after implementing a hospital-based cardio-respiratory rehabilitation program compared to a home-based Cardio-respiratory Physical Activity Program in patients with intervened CHDs. **Methods**: This is a randomized controlled trial on the effectiveness of two different rehabilitation programs on respiratory function, exercise capacity, and quality of life in patients with CHDs conducted at the Child Cardiology and Congenital Heart Disease Unit of the University Hospital Complex of A Coruña (CHUAC). There will be two groups: Cardio-respiratory rehabilitation group program conducted in a face-to-face format at the hospital (*n* = 26) and a study group that follows a home-based Cardio-respiratory Physical Activity Program (TELEA) (*n* = 26). The measurement variables will be respiratory function, forced vital capacity (FVC), forced expiratory volume in the first second (FEV1), maximum expiratory flow (PEF), the Tiffeneau index (FEV1 /FVC), forced expiratory flow (FEF25%, FEF50%, FEF75%, FEF25–75%), exercise capacity (peak VO_2_), and the quality of life of these children and their families. **Conclusions**: The implementation of cardiac and pulmonary rehabilitation programs in children with CHDs is essential to improve their quality of life, exercise tolerance, and socialization. These programs optimize life expectancy and promote integration, being crucial for their physical and emotional well-being

## 1. Introduction

Congenital heart defects (CHDs) are structural heart malformations present at birth and represent one of the leading causes of neonatal morbidity and mortality [1]. These anomalies are associated with significant health burdens [2], affecting approximately 1% of newborns. While the precise etiology of CHDs remains largely unknown, approximately 70–80% of cases result from interactions between genetic susceptibility and environmental factors, including maternal health conditions and teratogenic exposures during gestation [3,4].

Advances in medical and surgical management over the past four decades have significantly improved survival rates, with current data indicating that approximately 85% of children with CHDs survive into adulthood, including those with complex defects [5]. The improved survival outcomes, however, do not fully resolve challenges related to quality of life, life expectancy, or comorbidities. Children with CHDs often experience limited exercise capacity due to residual hemodynamic abnormalities and reduced pulmonary function, with a restrictive lung pattern being the most prevalent impairment [6]. Although to a lesser extent, some children may develop obstructive or mixed patterns resulting mainly from surgical manipulation or prolonged use of mechanical ventilation. Lung function deficits, particularly when moderate to severe, are independent predictors of mortality in adult CHD patients [7]. A sedentary lifestyle, frequently imposed on these children due to perceived fragility, exacerbates physical deconditioning and worsens cardiovascular outcomes.

Cardiac rehabilitation programs (CRPs) have demonstrated significant benefits in improving quality of life, exercise capacity, emotional well-being, and self-esteem in CHD patients. These programs also reduce morbidity and mortality in both the short and long term, with minimal reported adverse effects [5,8,9,10,11]. Despite these benefits, the availability and implementation of CRPs for pediatric CHD patients remain insufficient [12]. Pediatric CRPs present unique challenges, requiring family engagement and coordination among multidisciplinary teams experienced in managing CHDs. Effective communication with families is critical for ensuring adherence, particularly in hospital-based programs. While home-based CRPs offer cost advantages for healthcare systems, their effectiveness requires further validation [13,14,15].

Most pediatric CRPs rely on recreational exercise, such as sports (e.g., basketball, dancing, running, or swimming), stretching, and low-resistance weight-bearing activities [11,12,13,14,15,16]. However, restrictive lung dysfunction—a common finding in CHD patients, especially those undergoing cardiothoracic surgery—compounds exercise limitations. Its prevalence increases with younger surgical age and the number of thoracotomies performed [17]. Such pulmonary limitations, including reduced forced vital capacity, are closely linked to diminished exercise capacity, the strongest predictor of survival in this population [18,19].

### Main and Secondary Objectives

Main Objectives:To evaluate whether our proposed cardio-pulmonary rehabilitation program improves respiratory function and exercise capacity.To compare outcomes between the hospital-based rehabilitation group and the home-based rehabilitation group.

Secondary Objectives:To identify whether this specific CRP achieves higher adherence rates compared to other programs reported in the literature.To determine if adverse effects occur during or after completing the program.To verify whether the program has been conducted in a safe environment and assess its feasibility in natural settings.To determine if the program leads to improvements in the quality of life of these children and their families.

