#### 2.1.2. Exclusion Criteria

Patients with acute, inflammatory, or infectious health conditions that could pose a risk to them during the program.Patients who have undergone at least one interventional procedure or surgical intervention in a period of no less than 6 months before the start of the study.Lack of cooperation from the child due to immaturity or inability to understand or follow simple instructions required for evaluation or CRP.Lack of motivation from the patient or their guardians.Patients with comorbidities alongside CHDs that may influence exercise capacity or ventilatory function, or prevent participation in the program, such as acute inflammatory or infectious diseases.Withdrawal of informed consent.

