○The intervention will be carried out once a day. Duration: 15 min. Each patient will report the completion of the program through the TELEA platform. TELEA is a remote healthcare platform. This platform enables healthcare professionals to monitor and track the health status of patients in their homes, facilitating communication and reducing the need for hospital or clinic visits. Through TELEA, patients can record their vital signs and other health data, which are monitored in real-time by healthcare professionals. TELEA supports communication via videoconferencing and other digital tools, for instance, the video tutorial of the exercise home program, enhancing accessibility and the quality of healthcare services. Children will carry out the home program following the exercises of the video tutorial (Figure 1).Aerobic interval training: Patients will be monitored during physical exercise with a Heart Rate Monitor with ANT and Bluetooth wireless technology (HRM-Dual™), Garmin Ltd., Olathe, KS, USA. Legally domiciled in Schaffhausen, Switzerland) and GPS running watch Forerunner 45S (GARMIN^®^ Ltd., Olathe, KS, USA. Legally domiciled in Schaffhausen, Switzerland). The child will work within the heart rate ranges established after performing ergo-spirometry. Moderate intensity exercise closest to the first ventilatory threshold (VT1) will be performed. Gradually, based on the monitored child’s tolerance and their perception on the Modified Borg scale (0–10), the heart rate will progressively shift towards the second ventilatory threshold (VT2). They and their families will be taught to identify the symptoms and signs to stop physical exercise, just like the control group. Patients will download their heart rate and Modified Borg scale data after each session and can establish contact through the TELEA platform with the nursing staff of the cardiac rehabilitation unit at all times to resolve any questions they may have. Children in this group will not perform continuous aerobic exercise. They will perform interval aerobic exercise through bodyweight-based strength endurance training, following the same physiological principles explained for the control group. Exercises like wide squat, dynamic lunge, high pitch, jump, butt kicks, etc., will be performed. Some of them are shown in Figure 1 and Figure 2. Duration: 40 min.Stretching Exercise Program and Cool-down Exercises: to conclude the program, stretching exercises will be performed just like the control group. Duration: 5–10 min.Total duration of the complete program: approximately 1 h.(Figure 1 and Figure 2).

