
**Table 2 jcm-14-00816-t002:** Evaluation protocol.

Measurements	Variable	Material and Methods	Unit of Measurements	Measurements	
				Pre	Post
Lack of adherence to the protocol	Absence	Absence in more than 20% of the sessions	Absence equivalent to missing 5 out of the 24 planned sessions		
Anthropometric data	Circumference of body	Flexible tape measure	cm	X	X
	Composition	Bioelectrical impedance	% body fat	X	X
	Height	Height meter	m/cm	X	X
	Weight	Bascule	kg	X	X
Ergo-spirometry	Oxygen consumption	Ergometer and Treadmill	VO_2_	X	X
Respiratory function	FEV1, FVC, FEV1/CVF, PEF, FEF25%, FEF50%, FEF75%, FEF25–75%	Spirometry	%	X	X
	Respiratory Pattern		Restrictive, Obstructive, and mixed	X	X
Perceived effort	Effort	Modified Borg scale	0–10	X	X

Note: m = meter; cm = centimeter; kg = kilogram; FEV1 = Forced expiratory volume in 1 s; FVC = Forced vital capacity; FEV1/CVF = Tiffeneau index; PEF = maximum expiratory flow; FEF = forced expiratory flow.

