The success of CRPs relies on the collaboration of multidisciplinary healthcare teams with specialized expertise and addressing the high associated costs. Adherence challenges are particularly prevalent in hospital-based CRPs, which is why home-based programs are increasingly favored. These home interventions not only reduce costs but also diminish the burden on families. The challenge remains to demonstrate that the benefits in quality of life and functional outcomes are at least equivalent to those achieved in clinical settings [13,14,15].

Incorporating respiratory physiotherapy into CRPs is logical, given that CHD patients often experience impaired pulmonary function, contributing significantly to morbidity and mortality. These impairments are frequently due to restrictive respiratory patterns resulting from thoracotomies, sternotomies, and ventilatory muscle weakness, which collectively worsen lung function [41]. Exploring the potential of specific respiratory physiotherapy techniques, such as volumetric incentive spirometry and IMT, in conjunction with physical exercise, could strengthen respiratory muscles and address cardio-respiratory dysfunction in this population. Although preliminary studies have begun to evaluate the effects of IMT on lung and exercise capacity in pediatric CHD patients [28,42], research remains limited. We propose expanding CRPs to include targeted interventions for enhancing inspiratory volume, and strengthening ventilatory muscles may have broader implications for improving the health status of pediatric CHD patients. Given the scarcity of research in this area, further investigations are required to establish a foundation for optimizing rehabilitation strategies.

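### The only objective that names adherence compares the programme with unspecified published programmes; the randomised hospital-versus-home difference should be named instead, as an estimate with a 95% CI.

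*Protocol article*

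**What the plan says.** Under Main and Secondary Objectives, the one objective that names adherence is to identify whether the programme "achieves higher adherence rates compared to other programs reported in the literature". A main objective in the same section is general: "To compare outcomes between the hospital-based rehabilitation group and the home-based rehabilitation group". It does not mention adherence.

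Table 2, in the Outcomes section, has a row for lack of adherence. It sets one threshold for all participants, more than 20% of sessions missed, which it also gives as "Absence equivalent to missing 5 out of the 24 planned sessions". Sections 2.2.1 and 2.2.2 schedule two sessions weekly over 12 weeks in each arm. Section 2.6 plans a chi-square test for categorical variables without listing them.

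Three features bear on the adherence rate. Section 2.1.2 excludes "Lack of motivation from the patient or their guardians" and children who cannot cooperate with the evaluation or the programme. Section 2.5 offers travel help to families from outside the municipality in both groups. Section 3.1 describes travel help for the in-person group.

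On recording, hospital sessions are supervised by staff (Section 2.2.1). For the home arm, Section 2.2.2 states "Each patient will report the completion of the program through the TELEA platform" and, for the exercise sessions, "Patients will download their heart rate and Modified Borg scale data after each session".

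**The concern.** A comparison with published programmes is not randomised. A difference from them mixes the effect of the programme with differences in who was enrolled, what support families received and how adherence was counted. Here the entry criteria remove families likely to attend poorly, and travel help removes one barrier to attending. With no benchmark programme or rate stated, a reader could not tell what a higher rate was higher than, or why.

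The trial randomises children between hospital and home delivery of programmes with the same number of sessions, so it can say something firmer about adherence than the stated objective asks. If the objective is followed as written, the report could claim better adherence than the literature on grounds the design cannot support, and the randomised contrast could go unreported or appear only as an unplanned analysis.

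**Working it through.** **1. The plan's own figures.**
- Sessions: 2 × 12 = 24 in each arm.
- Threshold: 0.20 × 24 = 4.8, so 5 missed sessions (5/24 = 20.8%) is the first count above 20%. Table 2 is coherent and applies equally to both arms.
- Sample size (Section 2.4: d = 0.8, alpha 0.05, power 80%): a two-sided two-sample t-test needs n = 25.52, so 26 per group, as stated. This calculation is not for adherence.

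**2. What the literature comparison can show.** The documents give no benchmark rate, so the bias cannot be sized. Sampling error alone, at an assumed 80% adherence, is:
- one arm of 26: 1.96 × √(0.8 × 0.2/26) = 0.154
- both arms pooled, 52: 1.96 × √(0.8 × 0.2/52) = 0.109

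These limits of ±15 and ±11 points look tighter than those of the randomised comparison below, but they carry nothing for selection or for differences in definition.

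**3. Precision of the randomised comparison, 26 per arm.** Adherence rates and SDs are assumptions, because the documents give none.

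Proportion adherent, half-width = 1.96 × √(2p(1−p)/26):

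| Assumed p | Half-width |
|---|---|
| 0.9 | 0.163 |
| 0.8 | 0.217 |
| 0.7 | 0.249 |
| 0.6 | 0.266 |

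Mean sessions completed of 24, half-width = t(0.975, 50) × SD × √(2/26) = 2.009 × 0.2774 × SD = 0.557 × SD:

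| Assumed SD | Half-width (sessions) |
|---|---|
| 3 | 1.67 |
| 4 | 2.23 |
| 6 | 3.34 |

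Chi-square power at 26 per arm is 17% for 90% against 80%, 44% for 90% against 70%, and 35% for 80% against 60%. The last contrast would need 82 per arm for 80% power.

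**4. Why recording matters even with randomisation.** Randomisation balances the children, not how completion is recorded. As an illustration, assume independent sessions and a true completion probability of 80% per session in both arms. The proportion missing 4 or fewer of 24 is P(Bin(24, 0.20) ≤ 4) = 46%. If 25% of missed home sessions were recorded as done, the apparent miss rate is 0.20 × 0.75 = 0.15, and P(Bin(24, 0.15) ≤ 4) = 71%. At 10% over-reporting the figure is 56%. The over-reporting rates are assumptions; the document gives no evidence on them.

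**The case against.** The strongest reply is that nothing prevents the between-arm comparison. A main objective compares outcomes between arms, the Outcomes section points to Table 2, adherence is in that table, and a test for categorical data is planned. This stands. A reader might infer that the literature comparison replaces the randomised one; the document does not say so. It leaves the randomised one unnamed.

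A reader might also infer that each arm has its own yardstick. Table 2 has a single threshold on a common 24 sessions. The sentence on reporting completion through TELEA follows the daily 15-minute device work, and its hospital counterpart in Section 2.2.1 is also self-report, a diary. For exercise sessions the home arm has downloaded heart-rate data. The document never says that home absence is judged by self-report. Which record counts is a detail an article may leave to the full protocol. What remains is that staff witness sessions in one arm only.

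Nor does the document show that the literature comparison will be biased. The published programmes may have been equally selective, so it is open to bias of unknown size.

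Finally, Section 3 says "Adherence challenges are particularly prevalent in hospital-based CRPs, which is why home-based programs are increasingly favored", which might be read as making adherence the trial's hospital-versus-home question. The same paragraph frames the remaining challenge as equivalence in quality of life and function, and also cites cost and family burden.

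**Conclusion.** The point holds in a limited form. The only objective that names adherence uses an external comparator with no benchmark, in a trial whose entry criteria and travel help favour attendance, so a favourable answer could not be attributed to the programme. The randomised comparison is supported by the design and permitted by the general objective, but it is not named.

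The size of the selection bias cannot be derived from the document. The randomised estimate would carry about ±22 percentage points at an assumed 80% adherence (±16 to ±27 for 90% down to 60%), or ±1.7 to ±3.3 sessions for an assumed SD of 3 to 6, with 26 analysed per arm. It is also not free of bias in itself, because hospital and home sessions are not observed in the same way. This is a secondary objective, and no conclusion on respiratory function or exercise capacity depends on it.

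**What to change.** Reword the secondary objective along these lines: to estimate the difference in adherence between the hospital and home arms, as sessions completed of 24 and as the proportion meeting the Table 2 non-adherence definition, each with a 95% CI. Present literature rates as descriptive context, without a claim of superiority.

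Report home completion from all available records. As a sensitivity analysis, repeat it counting only sessions with a downloaded heart-rate recording. The recording-only count should not be the main definition: device or upload failures would then count as missed sessions in the home arm alone, replacing one asymmetry with another.

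The cost is one reworded objective and one extra tabulation from data already collected, with no change to treatment, schedule or sample size. The drawback is low precision, so the result should be stated as an estimate, and a non-significant difference should not be read as equal adherence.

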## 2. Materials and Methods

A parallel randomized controlled trial with a simple assignment has been designed (1:1) to test the effect of a 12-week specific CRP on respiratory function in pediatric patients with intervened CHDs. The trial will be conducted at the Teresa Herrera Maternal and Child Hospital of the University Hospital Complex of A Coruña (CHUAC) and follow the Consolidated Standards of Reporting Trials (CONSORT) Statement [20]; the treatment protocol is described in accordance with the recommendations of SPIRIT [21].

### 2.1. Study Participants and Setting

Study participation will be voluntary. Each potential participant will receive detailed information regarding the study objectives and methodological procedures prior to providing written informed consent.

#### 2.1.1. Inclusion Criteria

Individual case evaluation will determine eligibility for the Cardiac Rehabilitation Program (CRP). The pediatric cardiologist will assess each case and make decisions in conjunction with the patient’s family and the child or adolescent.

Participant selection will be based on the following criteria:Pediatric patients with a history of cardiac transplantation or CHDs who have undergone at least one interventional procedure or surgical intervention, at least 6 months before the start of the program in a state of clinical stability, hemodynamic stability, and ECG stability (ambulatory patient and does not require inotropic support or other therapies). They should have residual hemodynamic defects of sufficient severity that potentially restrict participation in physical activities, and their perception of fragility may be influenced by the social, family, school environment, or by the patient themselves.Children aged 8–17 years at the start of the study.Present a maximum oxygen consumption figure (peak VO_2_) below 80% of that predicted in ergo-spirometry performed prior to the start of the intervention program (in no case more than 6 months before the start).Patients who do not present contraindications for carrying out the program after evaluation in consultation with a pediatric cardiologist and a rehabilitation doctor.

#### 2.1.2. Exclusion Criteria

Patients with acute, inflammatory, or infectious health conditions that could pose a risk to them during the program.Patients who have undergone at least one interventional procedure or surgical intervention in a period of no less than 6 months before the start of the study.Lack of cooperation from the child due to immaturity or inability to understand or follow simple instructions required for evaluation or CRP.Lack of motivation from the patient or their guardians.Patients with comorbidities alongside CHDs that may influence exercise capacity or ventilatory function, or prevent participation in the program, such as acute inflammatory or infectious diseases.Withdrawal of informed consent.

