### 2.4. Sample Size

Since no information has been found on the magnitude of the effect on the topic studied, an effect size of 0.8 has been set, taking into account the scale proposed by Cohen and meta-analysis on the effect of rehabilitation in other respiratory conditions [37]. Sample size calculation was performed for a mean difference analysis of independent groups. The effect size was d = 0.8 alpha level of 0.05, power 80%. The estimated sample size was 26 subjects per group. Considering losses of 10%, the number of subjects needed was 56 subjects. G*Power 3.1 software was used to calculate the sample size.

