### 2.5. Randomization

Participants who meet the inclusion/exclusion criteria and wish to participate in the study will be randomly assigned to either the face-to-face treatment group or TELEA control group. We shall carry out a permutation block randomization (1:1) by generating a set of random numbers where the even numbers define a block of specified ordered random treatment assignments and the odd numbers define the other order of assignment of treatments. The random permuted blocks method should achieve balanced experimental groups. All children from outside the municipality’s constituency (from both groups) will be offered financial help to travel to the hospital.

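### Read literally, the exclusion criterion on prior procedures repeats the inclusion criterion, so the same fact both qualifies and disqualifies a child

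*Protocol article*

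**What the plan says.** Four places in the protocol article bear on this point.

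- **2.1.1 Inclusion Criteria** names the population as "Pediatric patients with a history of cardiac transplantation or CHDs who have undergone at least one interventional procedure or surgical intervention". The timing clause asks for patients "who have undergone at least one interventional procedure or surgical intervention, at least 6 months before the start of the program".
- **2.1.2 Exclusion Criteria** removes patients who have "undergone at least one interventional procedure or surgical intervention in a period of no less than 6 months before the start of the study".
- **2. Materials and Methods** gives the aim as the effect of the program on "respiratory function in pediatric patients with intervened CHDs".
- **2.5 Randomization** applies both lists: "Participants who meet the inclusion/exclusion criteria and wish to participate in the study will be randomly assigned".

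No other section restates either timing rule or says which one prevails.

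**The concern.** An exclusion criterion normally removes some of the patients whom the inclusion criteria admit. Here the exclusion sets the same lower bound, on the same kind of event, as the inclusion. A child who qualifies through an old procedure is disqualified by that same procedure.

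What is at stake is whether eligibility can be applied and audited. To enrol almost any child, a screener has to set a written exclusion aside or read it as meaning something else, and two screeners may resolve it differently. A monitor who applies the text as printed could log nearly every enrolment as an eligibility deviation. A reader of the results could not tell from the protocol which timing rule defined the sample.

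**Working it through.** The plan gives no figure on this point, so there is none to reproduce. The planned sample size does not enter the argument. The check is one of logic, supported by a small enumeration.

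**Inputs.** For each procedure let *m* be the number of months before the start.

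| Criterion | Section | Condition as worded | Counted back from |
|---|---|---|---|
| Inclusion | 2.1.1 | at least one procedure with *m* ≥ 6 | start of the program |
| Exclusion | 2.1.2 | at least one procedure with *m* ≥ 6 | start of the study |

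**Step 1: both dates the same.** Eligible = inclusion and not exclusion = (some *m* ≥ 6) and not (some *m* ≥ 6), which is empty.

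As a check, take every history of 0 to 3 procedures at 0 to 24 whole months before the start:

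- All histories: 1 + 25 + 325 + 2,925 = 3,276.
- Histories with no procedure at 6 months or more: 1 + 6 + 21 + 56 = 84.
- Histories meeting the inclusion timing: 3,276 − 84 = 3,192.
- Of these, not excluded: 0.

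The grid is hypothetical. The counts test the logic and do not estimate proportions of real children.

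**Step 2: different dates.** Suppose the program starts *L* months after the study. The article gives no value, so *L* is an assumption. A procedure then satisfies the inclusion without triggering the exclusion only if 6 − *L* ≤ *m* < 6, with *m* counted from study start. Every other procedure of that child must also have *m* < 6.

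| *L* (months, assumed) | Whole months that pass |
|---|---|
| 0 | none |
| 1 | 5 |
| 2 | 4, 5 |
| 3 | 3, 4, 5 |

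**Step 3: transplant patients.** The inclusion sentence can be parsed so that the procedure and timing clause attaches only to CHDs. On that reading, a child whose only procedure was a transplant less than six months earlier meets the inclusion and is not caught by the exclusion. A child with an older transplant is still caught, if a transplant counts as a surgical intervention.

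**Step 4: an old repair plus a recent re-intervention.** Of the 3,192 histories, 1,539 have every procedure at 6 months or more. The other 3,192 − 1,539 = 1,653 combine an old procedure with one under 6 months.

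| Treatment of the exclusion line | Combined histories passing (of 1,653) |
|---|---|
| As printed (some *m* ≥ 6) | 0, removed by the old procedure |
| Sense inverted (some *m* < 6) | 0, removed by the recent procedure |
| Ignored or deleted | 1,653 |

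**The case against.** The strongest reply is that the intent can be recovered. The Abstract and the Materials and Methods section both name children with treated CHDs as the population, and 2.1.1 positively requires the procedure. An exclusion that removes the whole named population cannot be what was meant. It reads like a garbled look-back window over the six months before the start, and on that reading it complements the inclusion. This stands as the most likely explanation, but it remains an inference. The printed rule is binding under 2.5, and nothing in the article corrects it.

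Three stronger readings are tempting, and the document does not support them.

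- **That the trial has no eligible child, to be set against the planned sample.** The differing anchors and the transplant reading leave narrow exceptions, and the intended population is evident. No effect on recruitment, power or analysis has been shown.
- **That the criteria as written admit a child with an old repair and a recent re-intervention.** Step 4 shows that the exclusion removes this child both as printed and with its sense inverted. The gap opens only if the line is ignored or deleted.
- **That a safety interval is left undefined.** The article never calls the six months a safety interval. Section 2.1.1 also requires clinical, hemodynamic and ECG stability, case-by-case evaluation, and no contraindication after review by a pediatric cardiologist and a rehabilitation doctor. These do not replace a timing rule, but a recently operated child does not simply pass.

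**Conclusion.** The two timing criteria contradict each other as worded. With a common start date, every child who meets the inclusion timing is excluded. With different start dates, only a window as wide as the lag between them survives (months 3 to 5 for an assumed lag of three months), plus possibly recent transplant patients on one parsing. The literal text therefore excludes nearly all of the intended population, though not strictly all of it.

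This rests on the plain meaning of the two sentences, both of which are complete in the article, and on 2.5 making both lists binding. It is most probably a drafting slip, so the finding is that the eligibility text cannot be applied as written. It is not a finding that the trial lacks a population. The use of two different anchor dates is a smaller inconsistency in the same pair of sentences.

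**What to change.** The sponsor should reconcile 2.1.1 and 2.1.2 in one amendment or erratum:

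1. Reword the criteria so that the exclusion no longer overlaps the inclusion.
2. Count both from one anchor date, either the study or the program, and say whether it is the child's own start.
3. Have the clinical team state which procedure the interval counts from when a child has had several, and whether the timing clause applies to transplant patients.

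Deleting the exclusion line is not enough by itself, because it leaves the third point open. That point also matters for the analysis. Section 2.1.1 accepts a baseline ergo-spirometry up to six months old, so if the line were simply deleted, a procedure could fall between the baseline test and the start of training. The pre-to-post change would then mix the two effects.

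This review does not say which interval or rule is right. The cost is about one sentence of text, with no change to the sample size, randomization or analysis.
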